#### Implementation factors

##### Achieving lifestyle goals and adverse effects

Lifestyle coaches continuously monitor personal lifestyle goals and potential adverse effects during the program. Goals are established at intake and are regularly assessed, reported, and modified in individual coaching sessions.

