### Intervention

GOAL! provides multidisciplinary support from registered allied health professionals and peer support workers. In a two-year program, participants receive group-based and individual support on different lifestyle behaviors. The program is divided into the guidance phase (first year), and the maintenance phase (second year) (Fig. 1).

The program starts with an intake session of 60 min conducted by the lifestyle coach, during which lifestyle behaviors, health outcomes, and individual needs are examined. Lifestyle goals are set through shared decision making, a collaborative process proven to enhance effectiveness [42]. In the guidance phase (i.e., year one), the program starts with a 3-month basic course, which encompasses 36 group sessions, each lasting 60 min, guided by allied health professionals. This includes 2-weekly sessions on physical activity (24 sessions in total) and 1-weekly session on nutrition (12 sessions in total). To achieve sustainable lifestyle behavioral change, there is a close collaboration with local stakeholders, thereby facilitating a transfer to the community setting. Thereafter, the aftercare of 9 months starts, with a thematic session of 60 min every two weeks (18 sessions in total) guided by the lifestyle coach about other lifestyle-related topics. These themes can vary based on the needs of the group and include themes such as smoking, sleep, and stress. In the guidance phase, participants receive 8 h of individual support from the lifestyle coach. This coaching can be utilized at the discretion of the participant and is centered around their self-identified lifestyle goals. As the participants’ options, needs and goals evolve, the coaching is adjusted accordingly. Group and individual sessions include theoretical education, interactive elements, assignments, physical activity, and supplementary practical activities (e.g., supermarket visits).

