During the maintenance phase (i.e., second year), there are 3 group sessions of 90 min each, and 5 moments of individual support of 30 min each, both guided by the lifestyle coach. Participants are encouraged to continue their activities in the community setting while the lifestyle coach has a key role in communication and connection with community partners as needed. Following each phase, lifestyle coaches assess and evaluate the changes in lifestyle behaviors and health outcomes together with the participants, setting new goals accordingly through shared-decision making.

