##### Process evaluation

Attendance at group sessions, use of individual coaching sessions, and dropout are continuously monitored by the health professionals throughout the program. This monitoring allows for better evaluation of effectiveness and implementation by providing important data on participant engagement, adherence, and reasons for dropout. The implementation process of GOAL! is continuously evaluated through experiences from (potential) participants, healthcare practitioners, and stakeholders. Their input and feedback serve as the foundation for developing new strategies for both the GOAL! program itself and its implementation.

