**Intervention group only**						
Ongoing	Lifestyle goals		Goals achieved yes/no, and explanation	x		
Ongoing	Undesirable effects		Undesirable effects yes/no, and explanation	x		
T0, T3	Implementation factors ^a^	Measurement Instrument for Determinants of the Innovation (MIDI)	Facilitators and barriers related to the intervention		x	

^a^ Also assessed at healthcare practitioners and stakeholders involved in the implementation and collaboration of GOAL!

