Participants’ personal information will only be used for measurement purposes and to share general study results, as specified in the consent form. The data will be pseudonymized, personal information will be stored separately, and both will be accessible only to the research team. Access to the data requires two-factor authentication. Data is stored within the institution for 15 years, following national privacy laws, and will not be publicly released.

If participants in the GOAL! program decide to withdraw, they will be asked to remain in the evaluation for additional analysis. If participants withdraw their consent for the evaluation, any data collected prior to withdrawal will be stored in accordance with the data protocol and Dutch law but will not be used for analysis or publication.

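### Adverse effects are recorded only by the lifestyle coach and only during the program, so their capture depends on program contact and none is stated for people who leave the program but stay in the evaluation

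*Protocol article*

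**What the plan says.** The Abstract and the Outcome measures section both include adverse effects among what is examined. The section on achieving lifestyle goals and adverse effects names who records them: "Lifestyle coaches continuously monitor personal lifestyle goals and potential adverse effects during the program". In Table 1, under the intervention group only, the item is ongoing, is recorded as "Undesirable effects yes/no, and explanation", and carries one mark, in the lifestyle-coach column.

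The Intervention section describes contact with participants. The program opens with a coach-led intake and then a "3-month basic course, which encompasses 36 group sessions, each lasting 60 min, guided by allied health professionals". The 18 aftercare sessions that follow are attributed to the coach. Year 1 also offers 8 h of individual support from the coach, of which the article says: "This coaching can be utilized at the discretion of the participant". In year 2 "there are 3 group sessions of 90 min each, and 5 moments of individual support of 30 min each", all led by the coach.

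On leaving, Data collection and management says: "If participants in the GOAL! program decide to withdraw, they will be asked to remain in the evaluation for additional analysis". Process evaluation says: "Attendance at group sessions, use of individual coaching sessions, and dropout are continuously monitored by the health professionals throughout the program", and adds that this yields reasons for dropout.

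**The concern.** Monitoring described as continuous should not depend on whether a participant turns up. Here one role holds the task, and that role's scheduled contact is uneven over the two years and partly optional. Someone who takes up little coaching, or who leaves the program, has fewer stated occasions on which an adverse effect could be recorded.

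If adverse effects make people attend less or leave, recording is thinnest in the people of most interest, and the rate errs downward. The Discussion itself anticipates low adherence and high dropout in this population. A low count could then mean few adverse effects or little contact, and the data would not show which. The item is collected in the intervention group only, so no control-group figure could reveal the problem. The article hopes to inform scale-up, where a statement about harms would carry weight.

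**Working it through.** The article states no adverse-effect figure to reproduce, so the check sets the stated recording rule beside the stated contacts.

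**1. Basic course (months 1–3).** Physical activity 24 + nutrition 12 = 36 sessions, which matches the article's total. They are attributed to allied health professionals; none is attributed to the coach by name. Coach contacts in or around this period are the intake, the T0 and T1 assessments, and whatever individual coaching the participant takes up. Of the 8 h for the year, between 0 and 8 h could fall here; spread evenly (an assumption) it would be 8 × 3/12 = 2 h.

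**2. Year 1 as a whole.** Group sessions attributed by name to the coach: 18 of 36 + 18 = 54, or 33%. Coach hours by name: intake 1 + individual 8 + aftercare 18 = 27, out of 1 + 8 + 36 + 18 = 63 scheduled hours.

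**3. Year 2.** Scheduled coach contacts: 3 + 5 = 8, on average one per 52/8 = 6.5 weeks. The T3 assessment and the evaluation after each phase come on top, so this is not the full count.

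**4. Fixed assessments.** Data collection and management itemises what is collected from GOAL! participants.
- Coach, T0–T3: lifestyle behavior, physical health outcomes, lifestyle goals.
- Research team, T0–T3: psychiatric symptoms, quality of life, eating behavior.
- Research team, T0 and T3: healthcare utilization, somatic illness, work, implementation process.

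Adverse effects are in none of these lists.

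**5. After leaving the program.** The recording rule is limited to the program. Leavers are asked to stay in the evaluation, but by step 4 no evaluation item asks about adverse effects. The remaining source is the reason for dropout. It can show an adverse effect that caused the exit. It cannot show one arising later, and no link from it to the adverse-effect record is stated.

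**6. Can the under-count be sized?** Let d be the share who leave, s and l the true adverse-effect rates in stayers and leavers, and c the share of leavers' effects that is recorded. If all stayers' effects are recorded,

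captured share = [(1 − d)s + dcl] / [(1 − d)s + dl].

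The article gives none of d, s, l or c. As an illustration only, take d = 0.20, s = 0.10 and l = 0.30. The denominator is 0.08 + 0.06 = 0.14. With c = 0 the captured share is 0.08/0.14 = 57%; with c = 1 it is 0.14/0.14 = 100%. The answer is set by the assumed c, so no size can be claimed.

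**The case against.** Four arguments stand against the point.

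- **The coach may lead basic-course sessions.** A reader might infer that the coach leads none of the 36. The article does not say so. The Abstract has both group and individual sessions given by allied health professionals, and the Intervention section names only those professionals and peer support workers as providers, so the coach may well be counted among the former. What stands is that the coach is not named as leader there but is named for the aftercare in the same paragraph.
- **The coach may still see leavers.** A reader might infer that contact with them is lost. No text says this. Coaches carry out the physical activity and physical health measurements at T0–T3, so a leaver who stays in the evaluation may meet the coach at those points. What stands is that adverse effects are not on the list for those assessments.
- **Leaving because of harm already has a route.** Reasons for dropout are recorded. This is a real mitigation, but a partial one, for the reasons in step 5.
- **A condensed article leaves operational detail to the full protocol.** This holds for hand-over forms between session leaders and coach. It does not cover the rule itself: the article states who records, in the text and again in Table 1, and itemises the assessments without adverse effects.

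It is also tempting to say that harms are missed where they are most likely. The article has no information on when harms occur or whether any go unrecorded, so that is not supported.

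**Conclusion.** The point holds as a weakness in the stated recording rule. It is neither a demonstrated bias nor a contradiction in the article. As written, capture of adverse effects depends on program contact, and no collection is stated for people who leave the program and remain in the evaluation. The rate may therefore be too low, by an amount that cannot be computed from the article.

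This rests on two readings: that Table 1's single mark belongs to the coach column, which agrees with the text, and that the itemised assessment lists are complete for this item. If the full protocol already has another role ask about adverse effects, or has the coach ask leavers at T1–T3, the point reduces to a wording correction. The effectiveness analyses are not affected. The change is worth making because it is cheap and because any statement on harms will otherwise be hard to interpret.

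**What to change.** 1. In the section on lifestyle goals and adverse effects, in Data collection and management, and in Table 1, state that the research team asks the existing yes/no-and-explanation question at T1, T2 and T3 of every GOAL! participant still in the evaluation, including those who have left the program. The coach's ongoing record stays as it is.
2. In Process evaluation, add the same field to the attendance and dropout record that the health professionals already keep, with adverse effect as a coded reason for dropout.
3. Report the rate over all enrolled GOAL! participants in the evaluation whose data may be used. The article excludes data from those who withdraw consent for the evaluation. Show separately the number not assessed after leaving the program.

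The cost is one question at research-team contacts that already take place (or in the online survey offered at T1 and T2), one field on an existing record, and a short amendment. The downside is a small recording burden for session leaders and participants. No new visits or staff are needed. Study status has data collection under way and recruitment ending in the first half of 2025, so at submission later T1–T3 contacts were still to come. Participants already past a time point would have the question only from their next contact, and the report should say so.

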##### Barriers and facilitators

The Measurement Instrument for Determinants of the Innovation (MIDI) is used to assess the barriers and facilitators to the implementation of GOAL!. The questionnaire consists of 4 constructs related to the innovation (7 determinants), the user (11 determinants), the organization (10 determinants), and the socio-political environment (1 determinant). Determinants can consist of one or more items. The total score of a determinant can be a combined measure calculated as the mean of multiple items. Most items are scored on a Likert scale from 1 (totally disagree) to 5 (totally agree). This questionnaire is also assessed in healthcare practitioners and stakeholders. The constructs addressed vary among the different respondent groups. GOAL! participants are asked about the constructs of innovation and user, healthcare practitioners about all the constructs, and stakeholders about the constructs of innovation, organization, and the socio-political environment. The questionnaire is assessed at start (T0) and 24 months (T3). The MIDI is adapted according to the manual to measure the relevant determinants for implementation of GOAL!, to fit the different respondents (MIDI-GOAL! participants, MIDI-healthcare practitioners and MIDI-stakeholders), and the different assessment points (at the start and end). Thus, there are 6 different versions of the MIDI. The MIDI is used to gain insight into the determinants of the innovation, to learn and improve the program from experiences, and to better interpret health outcomes [60].

##### Process evaluation

Attendance at group sessions, use of individual coaching sessions, and dropout are continuously monitored by the health professionals throughout the program. This monitoring allows for better evaluation of effectiveness and implementation by providing important data on participant engagement, adherence, and reasons for dropout. The implementation process of GOAL! is continuously evaluated through experiences from (potential) participants, healthcare practitioners, and stakeholders. Their input and feedback serve as the foundation for developing new strategies for both the GOAL! program itself and its implementation.

#### Cost-effectiveness

The cost-effectiveness of GOAL! is determined through a Health Technology Assessment (HTA), using the outcomes of the TIC-P. To weigh the costs against health-related outcomes, the main outcome is the deterministic incremental cost-effectiveness ratio using the EQ-5D-3 L scores, resulting in the quality-adjusted life years (QALY). For further evaluation, we perform probabilistic sensitivity analyses to account for the uncertainty surrounding the parameters, resulting in cost-effectiveness planes. The QALY is the most commonly used outcome in the economic evaluation of medical interventions and captures the impact of GOAL! on both the quantity and quality of life [61].

**Table 1 Tab1:** Overview of assessment procedures, measurements and variables

Assessment points	Outcome measures	Measurements	Variables	Lifestyle coaches	Research team	
**Intervention and control group**						
T0	Demographic characteristics	Gender	Categorical		x	
		Nationality	-		x	
		Ethnicity	Categorical		x	
		Date of birth (age)	Years		x	
		Diagnosis	Categorical		x	
		Marital status	Categorical		x	
		Highest level of education	Categorical		x	
		Primary source of income	Ratio		x	
T0, T1, T2, T3	Physical activity and sedentary behavior	Simple Physical Activity Questionnaire (SIMPAQ)	Moderate-vigorous physical activity in min/week and sedentary time per day	x		
	Eating behavior	MijnEetmeter	Daily intake of nutrients and daily consumption according to the Dutch ’Wheel of Five’		x	
	Sleep	Scales for Outcomes in Parkinson’s Disease sleep (SCOPA-sleep)	Total scores for nighttime sleep quality and daytime sleepiness	x		
	Substance use	Alcohol, Smoking and Substance Involvement Screening Test Lite (ASSIST-Lite)	Total scores of tobacco, alcohol, cannabis, stimulants, sedatives and opioids and psychoactive use	x		
	Physical health	Weight	kg	x		
		Abdominal circumference	cm	x		
		BMI	kg/m^2^	x		
		Fat percentage	%	x		
		Blood pressure	mmHg	x		
	Psychiatric symptoms	Brief Symptom Inventory (BSI)	Total scores for 9 symptom dimensions: somatization, obsession-compulsion, interpersonal sensitivity, depression, anxiety, hostility, phobic anxiety, paranoid ideation and psychoticism		x	
	Quality of life	Euro-Qol-5D-3 L (EQ-5D-3 L)	Index score based on the Dutch tariff and VAS score		x	
T0, T3	Care and social costs	Treatment Inventory of Costs in Patients with psychiatric disorders (TIC-P)	Healthcare utilization, medication use, productivity loss and costs (€)		x	
**Intervention group only**						
Ongoing	Lifestyle goals		Goals achieved yes/no, and explanation	x		
Ongoing	Undesirable effects		Undesirable effects yes/no, and explanation	x		
T0, T3	Implementation factors ^a^	Measurement Instrument for Determinants of the Innovation (MIDI)	Facilitators and barriers related to the intervention		x	

^a^ Also assessed at healthcare practitioners and stakeholders involved in the implementation and collaboration of GOAL!

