### Sample size

The sample size calculation is based on changes in lifestyle behaviors and health outcomes, for which we used data from a previous study on inpatients in the Netherlands [19]. A sample size of 98 participants is necessary to detect an average effect (f^2^ = 0.15) in a linear regression analysis with 80% power, 95% confidence interval, and six variables in the model. After reaching consensus on feasibility with the collaborating region, it was decided to enroll 50 people to participate in the GOAL! program and recruit an equally sized control group.

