### Outcome measures

The primary outcome is the change in physical activity between participants of GOAL!, compared to participants who receive care as usual. Secondary outcomes focus on changes in other lifestyle behaviors, physical health, mental well-being, and healthcare and social costs. In addition, the achievement of lifestyle goals, adverse effects, and barriers and facilitators to implementation are examined. Implementation factors are also investigated among healthcare practitioners and stakeholders.

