### Data collection and management

All participants receive study information through a visual informed consent, using visual elements to explain the procedures, risks, and benefits of study participation, thereby enhancing understanding and communication. Additionally, they receive a written information letter, after which they are requested to provide permission by signing an informed consent form. Measurements are taken through semi-structured interviews, physical measurements, and online questionnaires at start (T0), and after 3 (T1), 12 (T2) and 24 months (T3).

For GOAL! participants, data collection will be conducted by the lifestyle coach and the research team. As this research follows innovative care, lifestyle coaches assess lifestyle behavior, physical health outcomes, and lifestyle goals at all four assessment points (T0-T3). This is part of the program but will also be utilized for research purposes. Lifestyle coaches will record examination results on hard-copy documents, which will then be transferred and securely stored by the research team. Trained researchers and research assistants administer additional questionnaires and measurements. These include psychiatric symptoms, quality of life, and eating behavior at all four assessment points (T0-T3), and healthcare utilization, somatic illness, work, and the implementation process only at the start and end of the program (T0 and T3). Research assistants undergo structured training by experienced research team members in conducting semi-structured interviews via research and interview protocols.

The research team collects all data from the control group. Lifestyle behaviors, physical health outcomes, psychiatric symptoms, and quality of life are evaluated at all four assessment points (T0-T3), whereas healthcare utilization, somatic illness, and work are evaluated only at the start and end of study participation (T0 and T3).

All surveys in this study are entered in, and facilitated by Castor EDC, a cloud-based research data management platform [62]. At T1 and T2, participants have the option to complete some questionnaires via an online survey, thus shortening or obviating the need for an interview with the research team (Table 1). Furthermore, healthcare practitioners and stakeholders receive an online survey regarding the implementation process at the start and the end of the program (T0 and T3). Their informed consent is obtained online.

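### Discrete untoward events such as injuries and hospital admissions are logged only in the GOAL! arm, so their count has no background rate to be read against

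*Protocol article*

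**What the plan says.** Under Outcome measures, after the primary and secondary outcomes, the article states: "In addition, the achievement of lifestyle goals, adverse effects, and barriers and facilitators to implementation are examined". The Methods paragraph of the abstract says the same.

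The subsection on lifestyle goals and adverse effects, under Implementation factors, assigns the task: "Lifestyle coaches continuously monitor personal lifestyle goals and potential adverse effects during the program". Table 1 agrees. Under its block heading "Intervention group only" it lists the variable "Undesirable effects yes/no, and explanation" as ongoing, with only the lifestyle-coach column ticked.

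For controls, Data collection and management states: "The research team collects all data from the control group". It then lists the items. At T0 to T3 these are lifestyle behaviors, physical health, psychiatric symptoms and quality of life. At T0 and T3 only, they are healthcare use, somatic illness and work. Adverse effects are not on the list.

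**The concern.** The Background describes a population with frequent physical comorbidity, a raised risk of hospitalization, psychiatric symptoms and medication side effects. Over 24 months some injuries, admissions and other serious health events will occur in both arms whether or not GOAL! has any effect. The study recruits 50 controls so that change under GOAL! can be set against change without it, yet for this type of event it collects nothing comparable from them.

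The Discussion says the results will inform decisions on implementing and scaling up the program. Without a control count, background events in GOAL! participants may be read as harm from the program, or real harm may be put down to background illness. The count gives no means of telling which.

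**Working it through.** The plan gives no event rate for adverse effects, so there is no figure of its own to reproduce. The check has three parts.

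**1. What each arm contributes**

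| Type of information | GOAL! arm | Control arm |
|---|---|---|
| Symptom scores, EQ-5D-3L, sleep, substance use, weight, waist, blood pressure | T0 to T3 | T0 to T3 |
| Healthcare use and productivity loss (TIC-P) | T0, T3 | T0, T3 |
| Somatic illness (Data collection and management; no row in Table 1) | T0, T3 | T0, T3 |
| Adverse or undesirable effects, yes/no with explanation | ongoing, by coaches | not listed |

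Outcome measures, Implementation factors, Table 1 and Data collection and management agree with one another. The one-arm recording is therefore a stated collection rule, not a detail lost when the article was condensed.

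**2. Whether the TIC-P fills the gap**

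- Inputs: recall of the past 3 months (Healthcare and societal costs); taken at T0 and T3 (Table 1); T3 at 24 months.
- Period covered after baseline: 24 − 3 = 21, so about months 21 to 24.
- Share of follow-up covered: 3/24 = 12.5%. Not covered: 21/24 = 87.5%.
- The 3-month basic course, with 24 physical activity sessions, runs in months 0 to 3 and lies wholly in the uncovered part.

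This assumes that the TIC-P would pick up an admission; the article gives only examples of its items. The recall period of the somatic illness item is not stated, so how much it would recover is unknown.

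**3. What recording in both arms would give**

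Arm size is 50 (Sample size: "it was decided to enroll 50 people to participate in the GOAL! program and recruit an equally sized control group"). The rates below are assumptions. At equal rates *p*, the 95% half-width for a difference is 1.96 × √(2*p*(1 − *p*)/50).

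| Assumed rate in each arm | Half-width (points) |
|---|---|
| 5% | 8.5 |
| 10% | 11.8 |
| 20% | 1.96 × √(0.32/50) = 1.96 × 0.080 = 15.7 |
| 30% | 18.0 |

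The Newcombe interval for 10/50 vs 10/50 is also −15.7 to +15.7 points. The normal approximation is rough at 5%.

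Power at a 20% control rate, by normal approximation with two-sided alpha 0.05: take 46.5% in GOAL!, so the pooled rate is (0.20 + 0.465)/2 = 0.3325.

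- SE under the null: √(2 × 0.3325 × 0.6675/50) = 0.0942
- SE under the alternative: √((0.20 × 0.80 + 0.465 × 0.535)/50) = 0.0904
- z = (0.265 − 1.96 × 0.0942)/0.0904 = 0.89, power about 81%

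So 80% power exists only for a rate well over twice the control rate.

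Under the present plan, 10/50 in GOAL! would be reported as 20% (Clopper-Pearson 95% CI 10.0% to 33.7%), and 0/50 would bound the GOAL! rate below 7.1% (two-sided 95%: 1 − 0.025^(1/50)). Neither can be turned into a difference.

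**The case against.** A reader might infer that harm goes uncontrolled altogether, so that the study pairs a controlled benefit with an uncontrolled harm. The documents do not support that. Worsening on the nine symptom dimensions, quality of life (including pain and anxiety/depression), sleep, substance use, weight or blood pressure would show as a between-arm difference at T1, T2 or T3. The gap is confined to discrete events.

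A reader might also infer that the coach alone decides whether GOAL! caused an event. No attribution rule is given. Coaches record yes/no with an explanation, and their records pass to the research team. Who judges causation is not stated.

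Third, the article promises no between-arm comparison of adverse effects. It files them with implementation factors, and controls have no program whose effects could be logged. This is correct, and there is no contradiction in the text. It does not supply a background rate for an outcome that the study says it examines.

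Fourth, recording events in both arms would not show what GOAL! causes. Allocation is not randomized, the arms come from different municipalities, and 50 per arm gives wide intervals. All of this stands, and it limits how the comparison may be reported. An imprecise descriptive contrast still tells more than a single count.

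Finally, safety reporting for controls may be described in the full protocol. That cannot be excluded, but the article's explicit list of control-group data and the Table 1 heading both point to one-arm recording.

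**Conclusion.** The point holds for discrete untoward events. They are logged in the GOAL! arm only, by the staff who deliver the program, and the one shared instrument most likely to catch an admission covers about 3 of the 24 months after baseline. The GOAL! event count will have no background rate beside it.

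The primary analysis is unaffected, and graded worsening in health is already compared between arms. This is a worthwhile, inexpensive improvement, not an error in the plan. The conclusion rests on the article's text. The ±16 points rests on an assumed 20% event rate in both arms; for assumed rates of 5% to 30% the half-width runs from about 8.5 to 18 points.

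**What to change.** Add one row to the part of Table 1 that covers both groups: injury, hospital admission or other serious health event since the last assessment, recorded as yes/no with date and explanation. Word it identically in both arms and do not ask about cause. Keep it to discrete events: a broader question on any new or worsened problem would draw a yes from many people in both arms and overlap with the symptom and quality-of-life scales.

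The research team, not the coaches, asks it at T1, T2 and T3 through the existing interviews or, where offered, the online survey. Include participants who leave the program but stay in the evaluation, since coach monitoring is described only for the duration of the program. Amend the adverse-effects subsection and Data collection and management to match.

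Report counts by arm with a difference and 95% CI, labeled descriptive and non-causal because of the non-randomized design and 50 per arm. Keep the coach log as a GOAL!-only listing.

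Cost: one more question at three contacts that already take place, with no extra visits. Recall is 3 months at T1, 9 at T2 and 12 at T3. Because data collection is already under way, some participants will need a catch-up question covering the period since start. For those already past T2 this means recall of up to 24 months, and their answers should be flagged or shown separately, particularly if the arms were recruited at different times. Regular coach contact may also prompt fuller reporting in the GOAL! arm, which the report should mention.

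For any period not collected in controls, state that adverse effects are descriptive for GOAL! participants only.
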